#### Lung compliance during mechanical ventilation

Static lung compliance is the change in volume for any given applied pressure and is derived as the ratio between tidal volume (*V*_t_) and the difference between plateau pressure and positive end-expiratory pressure (PEEP).

The absolute value and the change from baseline will be analyzed for static lung compliance by means of summary descriptive statistics at each time point through day 14, if patient is mechanically ventilated (controlled mechanical ventilation).

#### Murray lung injury score (LIS)

The absolute value and the change from baseline will be analyzed for Murray Lung Injury Score by means of summary descriptive statistics at each time point until day 7 if chest X-ray is available.

#### Sequential Organ Failure Assessment (SOFA)

The absolute value and the change from baseline will be analyzed for SOFA score by means of summary descriptive statistics at each time point until day 7.

#### Oxygenation ratio (P_a_O_2_/F_i_O_2_ ratio)

The absolute value and the change from baseline will be analyzed for oxygenation ratio (P_a_O_2_/F_i_O_2_) by means of summary descriptive statistics at each time point during first 7 days.

#### Ventilation parameters

The absolute value and the change from baseline will be analyzed for each ventilation parameter (ventilatory plateau pressure, *V*_t_, PEEP, respiratory rate, F_i_O_2_, PIP, mean airway pressure, peak airway pressure) by means of summary descriptive statistics at each time point through day 14 for patients mechanically ventilated (controlled mechanical ventilation, assisted breathing, non-invasive ventilation).

#### Driving pressure (*P*_plat_ − PEEP)

The absolute value and the change from baseline will be analyzed for driving pressure (*P*_plat_ − PEEP) by means of summary descriptive statistics at each time point through day 14 for patients mechanically ventilated (controlled mechanical ventilation, assisted breathing, non-invasive ventilation).

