### Outcomes {12}

The main objective of this study is to investigate the safety of solnatide administration. Therefore, no formal primary and secondary outcomes are defined. Safety will be assessed by a review of mortality, incidence of adverse events, and serious adverse events, as well as by analysis of relevant laboratory data and ECG. The following parameters will be taken into account when assessing the safety of solnatide:
Vital signs (i.e., heart rate, systolic and diastolic blood pressure, and temperature)Clinical laboratory (i.e., white and red blood cell count, hematocrit, hemoglobin concentration, platelet count, creatinine, sodium, potassium, chloride, blood urea nitrogen, bilirubin, aspartate and alanine transaminases, lactate dehydrogenase, amylase, lipase, C-reactive protein, creatine kinase, arterial pH, PaO_2_, PaCO_2_, bicarbonate, SO_2_ as well as urine pH, specific weight, appearance, color, nitrites, proteins, glucose, urobilinogen, bilirubin, ketones, hematic pigments, and leukocytes)12-lead electrocardiogramHemodynamic parameters (i.e., mean arterial pressure, pulmonary blood volume, cardiac index, and cardiac outputNeed for vasoactive drugs24-h fluid balanceConcomitant medicationsAll-cause deathsUtilization of extracorporeal treatmentsAdverse events and serious adverse events

The secondary objective of this study is to evaluate possible endpoints for a future Phase III pivotal trial. Such endpoints investigated in this study include:
Extravascular lung water indexPulmonary vascular permeability indexMurray lung injury scoreOxygenation ratioVentilation parameters (i.e., plateau pressure, tidal volume, positive end-expiratory pressure, peak inspiratory pressure, respiratory rate, F_i_O_2_, mean airway pressure, peak airway pressure, ventilation mode)Lung complianceVentilation-free daysDays of ICUDays of hospitalizationDriving pressureSequential organ failure assessment

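### Plateau and driving pressure are pooled over controlled, assisted and non-invasive ventilation, although compliance, built on the same pressure difference, is not; their change from baseline is therefore confounded by ventilation mode.

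*Protocol article*

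**What the plan says.** Three parts of the protocol article's statistical methods use plateau pressure, and they do not cover the same readings.

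- *Lung compliance during mechanical ventilation* defines static compliance as tidal volume over "the difference between plateau pressure and positive end-expiratory pressure (PEEP"). The summary runs "at each time point through day 14, if patient is mechanically ventilated (controlled mechanical ventilation"), so only one mode qualifies.
- *Ventilation parameters* covers plateau pressure: "The absolute value and the change from baseline will be analyzed for each ventilation parameter (ventilatory plateau pressure" and others), through day 14, "for patients mechanically ventilated (controlled mechanical ventilation, assisted breathing, non-invasive ventilation").
- *Driving pressure (Pplat − PEEP)* begins "The absolute value and the change from baseline will be analyzed for driving pressure" and names the same three modes and the same window: "through day 14 for patients mechanically ventilated (controlled mechanical ventilation, assisted breathing, non-invasive ventilation").

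All three are descriptive summaries of absolute value and change from baseline, with no test. *Outcomes {12}* lists driving pressure and the ventilation parameters among the candidate endpoints for a later Phase III trial. The recorded parameters there end with "mean airway pressure, peak airway pressure, ventilation mode", so mode is collected. It does not reappear in the *Ventilation parameters* analysis text, and neither pooled summary mentions a split by mode.

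*Statistical methods {20a}* applies no missing-data method to these endpoints and uses whatever assessments are available.

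**The concern.** Driving pressure is the denominator of static compliance. One section admits that quantity only under controlled ventilation; another admits it under any of three modes. From the time patients begin to wean, the two tables will describe different patients on the same day, although one quantity is computed from the other.

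Under controlled ventilation in a passive patient, the ventilator supplies the whole distending pressure. In assisted or non-invasive breathing the patient's own effort supplies part of it, so a ventilator reading of plateau minus PEEP is not the same measurement. This is general respiratory mechanics and is not stated in the article, but the restriction on compliance is consistent with it.

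The article expects patients to be sedated at entry (*Assessment of potential risks and benefits*; *Discussion*), so baseline readings will plausibly be mostly controlled while later ones are mixed. It also expects solnatide both to lower ventilatory pressures and to help weaning (end of *Solnatide (AP301)—clinical studies*; *Known potential benefits*). The pooled summary cannot separate these two effects. At stake is whether driving pressure and plateau pressure can be judged as Phase III endpoints, which is the trial's secondary objective.

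**Working it through.** No figure in the article belongs to this point, so there is nothing to reproduce. The check is a comparison of scope, followed by an illustration with assumed inputs.

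**1. Scope side by side**

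| Quantity | Modes summarised | Window |
|---|---|---|
| Vt / (Pplat − PEEP) | controlled only | through day 14 |
| Pplat | controlled, assisted, non-invasive | through day 14 |
| Pplat − PEEP | controlled, assisted, non-invasive | through day 14 |

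The window is identical and the pressure term is shared. Only the mode rule differs.

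**2. Effect of mode mix with identical lungs in both arms**

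Let g be the reading in assisted or non-invasive mode minus the reading under controlled ventilation for the same lungs, and let s be an arm's share of readings in those modes. If baseline readings are all controlled, the spurious mean change in an arm is s × g. The spurious difference between arms is (s_active − s_placebo) × g.

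Example: g = −4 cmH2O, s = 0.5 against 0.4. The changes are −2.0 and −1.6, a difference of −0.4 cmH2O with no change in any lung.

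Assumed range: g from −6 to +2 cmH2O, and a share on assisted or non-invasive modes 10, 20 or 40 points higher in the active arm.

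| g (cmH2O) | 10 points | 20 points | 40 points |
|---|---|---|---|
| −6 | −0.6 | −1.2 | −2.4 |
| −4 | −0.4 | −0.8 | −1.6 |
| −2 | −0.2 | −0.4 | −0.8 |
| 0 | 0 | 0 | 0 |
| +2 | +0.2 | +0.4 | +0.8 |

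The row at −6 is an outer edge. A fall from 14 to 8, for instance, would imply a support level of 8 cmH2O. *Ventilator-free days* counts CPAP breathing with support up to 8 cmH2O as unassisted, so if that definition carries over, such a patient would not be in the summary at all. A reading of 10 instead of 8 gives g = −4.

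**3. Is a 10-point imbalance plausible without a drug effect?**

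With 20 patients on a dose and 35 on pooled placebo, all still ventilated and a true share of 0.5 in both, the standard error of the difference in shares is √(0.25/20 + 0.25/35) = √0.0196 = 0.14. A gap of 10 to 14 points is ordinary chance, and more so once patients are extubated or die.

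**4. Selection, a separate effect**

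Patients who reach unassisted breathing leave the summary. Assume no mode effect on readings, half the patients at 10 and half at 16 cmH2O, and a proportion w of the low-pressure half already off the ventilator. The mean of those remaining is [0.5(1 − w) × 10 + 0.5 × 16] / [0.5(1 − w) + 0.5].

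- w = 0.3 (placebo): 11.5 / 0.85 = 13.53
- w = 0.5 (active): 10.5 / 0.75 = 14.00, difference +0.47
- w = 0.7 (active): 9.5 / 0.65 = 14.62, difference +1.09

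Here faster weaning raises the apparent driving pressure of the better arm.

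**5. After restriction to controlled ventilation**

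s = 0 in both arms, so the term in step 2 is zero. The selection in step 4 remains, because the summary still depends on who is left on controlled ventilation.

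**The case against.** The case for leaving the text alone has several parts.

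- **Direction.** A reader might infer that earlier weaning must show up as a fall in driving pressure. The article does not support that. It does not say how plateau pressure is obtained in assisted or non-invasive modes or that such readings are lower, and selection can push the mean up. This objection stands, and no direction is claimed.
- **Measurability.** A reader might also infer that plateau minus PEEP cannot be derived at all outside controlled ventilation. That goes too far. Measurement instructions may sit in the full protocol or the case report form, and where a site records no plateau the available-data rule simply leaves the value out. What remains is comparability: any value that is recorded enters the same mean as the controlled readings.
- **Reason for the compliance rule.** The article does not explain it, and compliance also uses tidal volume. It is fair that the rule does not prove the authors saw the problem. The difference in scope is unexplained either way.
- **Left to the SAP.** Subgroup analyses are deferred there, and a split by mode is not forbidden. But the article itself fixes which modes enter each summary, and it does so differently for the same quantity. That is a stated rule, not an omitted detail.
- **The remedy has its own bias.** True: controlled ventilation after baseline is a post-randomisation state. The counts requested below make this visible but do not correct it.
- **Small consequence.** Also true. There is no test and no decision rule attached to these tables.

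**Conclusion.** The point holds as a confounding problem of unknown direction. The article pools plateau pressure and driving pressure over three ventilation modes while limiting compliance, which uses the same pressure difference, to one. Because the mode mix changes with weaning, a change from baseline or an arm difference in these tables can arise with identical lungs.

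On the assumed inputs, the mode-mix effect lies between about −2.4 and +0.8 cmH2O, and it is zero if readings do not differ by mode. These are illustrations, not estimates: neither the mode gap nor the imbalance is in the article. The conclusion rests on two assumptions: that readings differ by mode, which is general respiratory mechanics, and that the mode mix differs between arms, which the expected drug effect and groups of 20 make likely.

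The correction is worth making because these are Phase III candidates. It does not affect the safety objective or any tested comparison.

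**What to change.** Reconcile the three sections.

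- In *Driving pressure*, and in *Ventilation parameters* for plateau pressure only, make the main summary the readings taken under controlled mechanical ventilation, as the compliance section does. Alternatively, present the summary separately by ventilation mode.
- Keep PEEP, FiO2 and respiratory rate for all modes.
- Beside each summary, show per arm and time point the number of patients in each mode, extubated and dead.

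The cost is analysis wording and some table columns, since mode is already collected. There will be fewer plateau and driving pressure values after the first days. The restricted summary also still conditions on who remains on controlled ventilation, so it should be read only with those counts.

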#### Spontaneous Breathing Trial

The time (in days) from the first spontaneous breathing trial to the first successful extubation / unassisted breathing will be calculated. Summary descriptive statistics will be provided.

In addition, patients will be classified according to the following outcome definitions [32]:
SimpleSuccessful SBT after the first attemptDifficultFailed SBT at first attempt andRequired up to three trials orRequired < 7 days to reach successful SBTProlongedRequired > 7 days to reach successful SBT

#### Time to extubation through day 28

Time to extubation (in days) is defined as the difference between the first extubation date and the randomization date. Patients still intubated at day 28 or who die while still intubated will be censored at day 28. Summary descriptive statistics will be provided for the time to extubation.

#### Ventilator-free days (VFD) through day 28

VFD is defined as the number of days from randomization to day 28 after achieving unassisted breathing for patients who maintained unassisted breathing for at least two consecutive calendar days. If a patient survived for more than 48 consecutive hours of unassisted breathing but required assisted breathing (for any reason) before day 28, the number of VFD is the number of days of successful unassisted breathing through day 28. All periods of successful unassisted breathing (> 48 consecutive hours) are taken into account. Unassisted breathing is defined as being extubated with face mask, with nasal prong oxygen or room air or T-tube breathing or tracheostomy mask breathing or CPAP breathing with ≤ 8 cm H_2_O pressure support of assisted ventilator support, according to weaning protocol. Patients who die before day 28 will be assigned the number of days of successful unassisted breathing. If a patient required more than 28 days of mechanical ventilation, the value for VFD will be set to 0.

The parameter of ventilator-free days will be analyzed by means of an analysis of variance (ANOVA) model with treatment cohort as an independent class variable. Mean estimates will be provided, together with their corresponding two-sided 95% confidence intervals.

No multiplicity adjustment for multiple comparison will be applied, given that statistical comparison will be performed only between the highest solnatide dose cohort and the placebo cohort. A statistical comparison between lower dose(s) and placebo will be performed only in case of statistical significance of the comparison between the highest solnatide dose cohort and the placebo cohort.

#### Days of hospitalization through day 28

Length of hospital stay (in days) is defined as the difference between the discharge date and the randomization date. Patients still in the hospital at day 28 or who die during hospitalization will be censored at day 28. Days of outpatient hospitalization will not be included. Summary descriptive statistics will be provided for the number of days of hospitalization.

#### Days of stay at ICU through day 28

Length of stay at ICU (in days) is defined as the number of calendar days a patient was in the ICU. Patients still in the ICU at day 28 or who die during the stay at ICU will be censored at day 28. Summary descriptive statistics will be provided for the number of days of stay at the ICU.
2.Safety analyses

Safety analyses will be conducted on the Safety Set and will be reported by actual treatment cohort. No methodology for missing data handling will be applied for safety parameters.

#### Drug-related adverse events through day 14

The incidence of treatment-emergent drug-related AEs through day 14 after randomization, both in terms of number of events and in terms of patients with at least one event, will be tabulated by MedDRA System Organ Class (SOC) and Preferred Term (PT).

#### All adverse events through day 28

According to the onset date of the event, AEs will be defined as follows:
Treatment-emergent AEs are those events with an onset date after treatment initiation;Non-treatment-emergent AEs are those events with an onset date between screening and treatment initiation.

Non-treatment-emergent adverse events will be listed only. The incidence of treatment-emergent adverse events (TEAE) will be tabulated by MedDRA System Organ Class (SOC) and Preferred Term (PT). The incidence of TEAEs will also be summarized by system organ class, preferred term, and severity (based on investigator’s judgment).

The same analysis will be repeated for SAEs regardless of drug relationship, for drug-related SAEs, AEs with an outcome of death, and AEs leading to discontinuation of treatment. Deaths reportable as SAEs will be listed by patient and tabulated by MedDRA SOC and PT.

#### All-cause deaths through day 28

The number and proportion of deceased patients will be reported. In addition, the time (in days) from randomization to the event will be used for analysis. Subjects without an event will be censored at the earlier of the last contact date or day 28. The Kaplan-Meier estimates of the survival functions for each treatment cohort will be plotted and summarized.

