## Objectives {7}

The main objective is to assess the local and systemic safety of 7 days orally inhaled sequential multiple ascending doses of solnatide in patients with pulmonary permeability edema and moderate-to-severe ARDS.

Secondary objective is to review potential efficacy endpoints for a future Phase III pivotal trial.

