## Statistical methods

### Statistical methods for primary and secondary outcomes {20a}

Data collected in this study will be listed and summarized as described below by treatment group. Data from all sites will be pooled and summarized. Continuous data will be summarized by mean, standard deviation (SD), median, first and third quartiles, minimum, and maximum. Categorical data will be presented by absolute and relative frequencies (n and %) or contingency tables. All statistical tables, listings, figures, and analyses will be performed by means of SAS® release 9.4 or later (SAS Institute, Inc., Cary, NC, USA).

A two-sided alpha level 0.05 will be considered. No alpha level adjustment will be made for secondary preliminary efficacy outcome variables and for multiple comparisons. Patients will be included in each analysis based on available assessments. No methodology for missing data handling will be applied, except for the EVLWI efficacy endpoint. Censoring rules for time-to-event analyses will be detailed in the Statistical Analysis Plan.

There is no primary efficacy endpoint as the primary objective of the study is to investigate the safety of solnatide. All efficacy analysis will be considered as secondary preliminary efficacy analyses. All secondary preliminary efficacy analyses will be performed based on the ITT set as primary analysis and on the PP set as supportive analysis and will be reported by planned treatment cohort.

No methodology for missing data handling will be applied for secondary preliminary efficacy endpoints, except for EVLWI. The homogeneity of treatment effects across different centers will not be tested.

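### Time to extubation ends at the first extubation of any kind, so failed extubations and extubations shortly before death are summarised as early liberation

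*Protocol article*

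**What the plan says.** All three weaning definitions stand together in the protocol article's statistical methods.

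- **Time to extubation through day 28.** The event: "Time to extubation (in days) is defined as the difference between the first extubation date and the randomization date". The exceptions: "Patients still intubated at day 28 or who die while still intubated will be censored at day 28". The analysis: "Summary descriptive statistics will be provided for the time to extubation".
- **Spontaneous Breathing Trial.** "The time (in days) from the first spontaneous breathing trial to the first successful extubation / unassisted breathing will be calculated". This clock stops only at a successful extubation or unassisted breathing.
- **Ventilator-free days (VFD) through day 28.** "All periods of successful unassisted breathing (> 48 consecutive hours) are taken into account". Shorter periods earn no credit.

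On the role of the endpoint, section {20a} says: "All efficacy analysis will be considered as secondary preliminary efficacy analyses". Objectives {7} gives their purpose: "Secondary objective is to review potential efficacy endpoints for a future Phase III pivotal trial". Section {20a} also leaves one matter to the analysis plan: "Censoring rules for time-to-event analyses will be detailed in the Statistical Analysis Plan". That defers censoring rules. The event itself is fixed in the article.

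**The concern.** A short time to extubation is naturally read as early liberation from the ventilator. Under the stated rule it can also mean that extubation failed, or that the patient was extubated and then died.

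The rule is also at odds with its surroundings. Moving deaths while intubated to day 28 shows that death is not meant to count as early liberation, yet a death just after extubation escapes that rule. The plan has a success criterion and uses it for the endpoints on either side, but not here. One patient can therefore show a short time to extubation and no ventilator-free days.

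The handling of death matters in this population. Background and rationale {6a} cites hospital mortality of 40.3% in moderate and 46.1% in severe ARDS. At stake is the reliability of a descriptive efficacy summary in a trial whose secondary objective is to look over endpoints for Phase III.

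**Working it through.** **Plan's own figure.** None is given for this endpoint. The only power statement, in Sample size {14}, concerns EVLWI: 20 per group, difference 3.2, SD 3.5, two-sided 0.05. A two-group t-test gives 0.804, which agrees with the stated 80%. Nothing below affects it.

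**Step 1: the definition applied to four patients.**

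| Course (example) | First-extubation sentence | Day-28 sentence |
|---|---|---|
| Extubated day 10, stays off | 10 | does not apply |
| Extubated day 7, fails, lasting extubation day 10 | 7 | does not apply |
| Extubated day 6, dies the same day | 6 | does not apply (not intubated at death) |
| Extubated day 4, reintubated, still intubated at day 28 | 4 | 28 |

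Rows 2 and 3 are the bias. Row 4 is an internal conflict: the two sentences give answers 24 days apart, and nothing says which governs.

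**Step 2: effect on an arm mean.** Take 20 patients per arm and let censored patients enter at 28 (an assumption, since the article gives only summary statistics). The shift is the sum of (intended value − scored value) divided by 20.

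- One patient extubated on day 6 before death: (28 − 6)/20 = 1.1 days.
- One failed attempt three days before the lasting one: 3/20 = 0.15 days.

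**Step 3: can the order of the arms change?** All counts are assumed.

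- Better arm: 12 lasting extubations on day 10, 8 deaths while intubated.
- Worse arm: 10 lasting extubations on day 10, 3 of them after a failed attempt on day 7; 10 deaths, 4 of them extubated on day 6.

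| | Better arm | Worse arm |
|---|---|---|
| Protocol rule, mean | (12×10 + 8×28)/20 = 17.2 | (7×10 + 3×7 + 4×6 + 6×28)/20 = 14.15 |
| Protocol rule, extubated | 12/20 | 14/20 |
| Lasting extubation, mean | 17.2 | (10×10 + 10×28)/20 = 19.0 |
| Lasting extubation, extubated | 12/20 | 10/20 |
| VFD, mean | 12×18/20 = 10.8 | 10×18/20 = 9.0 |

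The protocol rule reverses the order, while lasting extubation agrees with VFD. Of the 19.0 − 14.15 = 4.85 days, extubation before death supplies 4×22/20 = 4.4 and failed attempts 3×3/20 = 0.45. With the failed attempts alone the worse arm's mean is 19.0 − 0.45 = 18.55, still above 17.2, so there is no reversal.

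**Step 4: simulation over a range of assumptions.** Lasting extubation averages about day 13; patients extubated before death have that extubation spread evenly over days 2 to 28; failed attempts come 3 days early. The better arm has 40% deaths with neither problem: mean 18.86 days, 60% extubated. The worse arm has 50% deaths and no failed attempts:

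| Share of deaths extubated first | Extubated, protocol rule | Mean, protocol rule | Mean, lasting extubation |
|---|---|---|---|
| 0% | 50% | 20.4 | 20.4 |
| 20% | 60% | 19.1 | 20.4 |
| 40% | 70% | 17.8 | 20.4 |
| 60% | 80% | 16.5 | 20.4 |

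The slope of the mean is (20.4 − 16.5)/0.6 = 6.5 days per unit share, so it crosses 18.86 at (20.4 − 18.86)/6.5, about 24%. With 20% failed attempts added, the means are level at a 20% share (18.83 against 18.86). Failed attempts alone, in 10–20% of survivors, move the mean by only 0.15–0.29 days.

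**Step 5: the same practice in both arms** (30% of deaths extubated first, 15% failed attempts). Under the protocol rule the means are 17.06 and 18.23, a gap of 1.17 days; under lasting extubation they are 18.89 and 20.40, a gap of 1.51. The median gap falls from 8.6 to 2.4 days, although the larger figure is inflated because a median at 50% deaths sits at the day-28 limit. The order holds and the contrast shrinks.

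**The case against.** The strongest reply is that nothing rests on this summary. It is descriptive. The ventilation endpoint that is formally compared is VFD, which already requires more than 48 hours, and deaths are reported separately with Kaplan-Meier curves. A reader would see all three for the same cohort. This stands: no inference is affected.

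A reader might infer that the rule makes a worse arm look better on a designated Phase III endpoint. The document does not support that. The Phase III list in Outcomes {12} names ventilation-free days and not time to extubation; its opening is not exhaustive, but membership is an inference. The article never mentions extubation at withdrawal of support and gives no rate of failed extubation. Its exclusions (do-not-resuscitate orders, patients not expected to survive) plausibly make extubation before death rarer. Treatment is blinded, and with equal practice the order does not change.

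One counterpoint remains. Dose groups are enrolled one after another, recruitment is planned over about four years, and the 35 placebo patients come from all steps. If each dose is set against pooled placebo, practice could differ for reasons of calendar time. That is a possibility, not something the document shows.

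It may also be said that the analysis plan will settle the reintubated patient. For censoring that may be so, but the event is already fixed in the article.

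**Conclusion.** The point holds as a defect in a secondary definition. The rule counts failed extubations and extubations shortly before death as early liberation. It departs from the success criteria beside it and from the plan's own treatment of deaths while intubated, and it gives two answers for a patient reintubated and still intubated at day 28.

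The consequence is a biased descriptive summary; tests, power and sample size are untouched. Extubation before death carries most of the effect, and failed attempts alone carry little. Reversal of the arms is possible only if extubation before death differs between them. In the simulation it needs roughly a quarter of the worse arm's deaths, against none in the better arm. All such shares and counts are assumptions. It is worth correcting because the correction is cheap, not because a decision depends on it.

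**What to change.** 1. Define the event as the first extubation followed by more than 48 consecutive hours alive with unassisted breathing. Use the hours criterion explicitly, because the VFD paragraph also speaks of two calendar days.
2. Treat a patient reintubated within 48 hours as still intubated until a later successful extubation.
3. State that the day-28 sentence applies to patients with no successful extubation by then. This removes the conflict for reintubated patients.
4. Set patients who die by day 28 without a successful extubation to day 28. Handle death by day 28 after a longer extubation the same way, or as a competing event. The 48-hour condition alone would still count a patient who dies on the third day after extubation as an early success.
5. Keep the first extubation of any kind as a listing.

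The cost is one or two sentences and slightly fewer events. The dates are already needed for VFD and mortality. An extubation in the last two days of follow-up needs a stated rule, since 48 hours cannot be observed before day 28.

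### Ventilator-free days credit patients who die after weaning, so the score can rank a death above a survivor and understate harm from post-weaning deaths

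*Protocol article*

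**What the plan says.** The Protocol article, under Ventilator-free days (VFD) through day 28, opens with "VFD is defined as the number of days from randomization to day 28 after achieving unassisted breathing for patients who maintained unassisted breathing". On repeated weaning it says "All periods of successful unassisted breathing (> 48 consecutive hours) are taken into account".

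Two sentences fix the low end of the scale. On death: "Patients who die before day 28 will be assigned the number of days of successful unassisted breathing". On long ventilation: "If a patient required more than 28 days of mechanical ventilation, the value for VFD will be set to 0". The second is the only rule that sets a value of 0. No sentence gives 0, or a worst rank, to a patient who dies.

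The length of a successful period is given in two ways. The definition is "for patients who maintained unassisted breathing for at least two consecutive calendar days", while the later sentences require more than 48 consecutive hours.

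The analysis is also fixed: "The parameter of ventilator-free days will be analyzed by means of an analysis of variance (ANOVA) model with treatment cohort as an independent class variable". The highest dose is compared with placebo first, and lower doses only if that comparison is significant. VFD and the EVLWI change are the only efficacy endpoints for which the article plans a model-based comparison; the others are summarised descriptively. The Outcomes section lists ventilation-free days among the candidate endpoints for a Phase III trial.

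**The concern.** VFD is meant to combine time off the ventilator with survival. Under this rule, days off the ventilator count the same whether the patient then lives or dies. A patient weaned early who dies in the third week can outscore a survivor who weaned slowly.

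Deaths are common in this population. The Background gives hospital mortality of 40.3% in moderate and 46.1% in severe ARDS, and it attributes most ARDS deaths to multiorgan failure, which faster weaning need not prevent. Unassisted breathing, as defined, includes T-tube and tracheostomy-mask breathing, so patients who are still critically ill can accrue credited days.

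What is at stake is how the VFD comparison is read, and whether VFD in this form is carried forward as a Phase III endpoint.

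**Working it through.** The plan gives no power or effect figure for VFD, so there is none to reproduce. The check applies the stated rule, first to single patients and then to arms.

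**1. Single patients (rule only, no rates assumed)**
- Weaned on day 5, dies on day 20: 20 − 5 = 15 under the plan; 0 if death is scored 0.
- Survivor weaned on day 14: 28 − 14 = 14 under either rule.
- Survivor weaned on day 20: 28 − 20 = 8 under either rule.
- Survivor ventilated throughout: 0 under either rule.

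The patient who died ranks above all three survivors.

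**2. Dilution of harm**

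Suppose 15 percentage points more patients in one arm are weaned on day 8 and die on day 16, where they would otherwise have been weaned on day 8 and survived.
- A survivor scores 28 − 8 = 20. The patient who dies scores 16 − 8 = 8 under the plan and 0 if death is scored 0.
- Loss in the arm mean, plan's rule: 0.15 × (20 − 8) = 1.8 days.
- Loss in the arm mean, death = 0: 0.15 × 20 = 3.0 days.
- Share of the loss not seen under the plan: 1 − 1.8/3.0 = 40%.

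**3. Change of sign (assumed rates)**

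Let S be the share surviving, A the share dying after weaning, w the day of weaning and d the day of death after weaning. Deaths on the ventilator with no earlier weaned period score 0 under both rules.
- Plan's rule: mean = S × (28 − w) + A × (d − w)
- Death = 0: mean = S × (28 − w)

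Placebo, assumed: 40% deaths (35% on the ventilator, 5% after weaning), w = 12, d = 22.
- Plan: 0.60 × 16 + 0.05 × 10 = 10.1
- Death = 0: 0.60 × 16 = 9.6

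Dose, assumed: 50% deaths (35% on the ventilator, 15% after weaning), w = 10, d = 22.
- Plan: 0.50 × 18 + 0.15 × 12 = 10.8
- Death = 0: 0.50 × 18 = 9.0

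Dose minus placebo is 10.8 − 10.1 = +0.7 under the plan and 9.0 − 9.6 = −0.6 with death = 0.

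**4. How far this depends on the assumptions**

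Placebo and d = 22 are kept as above. The dose arm has 50% deaths throughout.

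| Dose arm: deaths on ventilator + after weaning, weaning day | Plan's rule, dose − placebo | Death = 0, dose − placebo |
|---|---|---|
| 45% + 5%, day 12 | 8.5 − 10.1 = −1.6 | 8.0 − 9.6 = −1.6 |
| 35% + 15%, day 12 | 9.5 − 10.1 = −0.6 | 8.0 − 9.6 = −1.6 |
| 35% + 15%, day 10 | 10.8 − 10.1 = +0.7 | 9.0 − 9.6 = −0.6 |
| 25% + 25%, day 12 | 10.5 − 10.1 = +0.4 | 8.0 − 9.6 = −1.6 |

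If only on-ventilator deaths rise, the two rules agree. If only post-weaning deaths rise, harm is diluted but keeps its sign. The sign turns when the dose also brings weaning forward, or gets more patients weaned who then die.

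**5. The two thresholds**

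A patient extubated at 20:00 on day 10 and reintubated at 06:00 on day 12 has 34 hours of unassisted breathing. This touches two consecutive calendar days before reintubation, but it is not more than 48 hours. The two wordings can classify this patient differently. The size of this effect cannot be computed from the document.

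**The case against.** The strongest reply is that a harmful dose looks better on VFD only in particular circumstances. Deaths on the ventilator with no earlier weaned period already score 0, and they may be the majority. The document does not say what share of deaths follows weaning, and the 40.3% and 46.1% are hospital mortality of every kind. This stands. A reader might infer that the plan will make a harmful dose look beneficial; the documents support only that it can.

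The effect is also small against the noise. In the scenario of step 3 under the plan's rule, the variances are 0.60 × 16² + 0.05 × 10² − 10.1² = 56.6 and 0.50 × 18² + 0.15 × 12² − 10.8² = 67.0. With 20 per arm the standard error is √(56.6/20 + 67.0/20) ≈ 2.5 days, before any spread in weaning days is added. The gap between the two rules, 0.7 − (−0.6) = 1.3 days, is about half of that. The rule will seldom decide the test in this trial. It matters more for the point estimate and for a larger trial that inherits the definition.

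A reader might also infer that deaths are hidden. They are not. All-cause death through day 28 is reported as counts, proportions and Kaplan-Meier curves by cohort, and dose escalation rests on the safety board's review, not on VFD.

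Finally, it is tempting to say that VFD and time to extubation treat death in opposite directions. They do not. For time to extubation the rule is "Patients still intubated at day 28 or who die while still intubated will be censored at day 28", so a death after extubation keeps its early extubation time, much as it keeps its days in VFD. Length of hospital stay does differ ("Patients still in the hospital at day 28 or who die during hospitalization will be censored at day 28"), and ICU stay follows the same pattern, but both measure something else and are only described.

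The choice of ANOVA over a rank test is not shown to be an error and is not part of this point.

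**Conclusion.** The point holds as a defect in the endpoint's definition. That the score can rank a patient who dies above a survivor follows from the stated rule without any assumption. Dilution also follows whenever deaths after weaning increase; in the worked example 40% of the loss disappears (1.8 against 3.0 days). Reversal of sign (+0.7 against −0.6 days) is possible but conditional. It rests on assumed mortality, an assumed post-weaning share of 5% vs 15% of patients, and earlier weaning on the dose.

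The consequence is a VFD comparison that can mislead and a candidate Phase III endpoint that may be misjudged. It does not affect the safety assessment. The change should be made, but the trial's main conclusion does not depend on it.

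The double wording of the success threshold is a real but minor inconsistency.

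**What to change.** In the section Ventilator-free days (VFD) through day 28:
- Replace the sentence on deaths with a rule that VFD is 0 for any patient who dies on or before day 28, and use this in the main VFD analysis.
- Keep the present rule as a named sensitivity analysis, so that the influence of post-weaning deaths can be seen.
- Use one success threshold, more than 48 consecutive hours of unassisted breathing, in place of the two now stated.

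The change should be dated before unblinding. It needs wording only: deaths through day 28 and ventilation periods are already required for planned analyses. The cost is a lower mean VFD. In the assumed scenario of step 3 it falls from 10.1 to 9.6 on placebo and from 10.8 to 9.0 on the dose; where few deaths follow weaning the drop is slight.

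Scoring death as 0 removes the inversion but does not turn VFD into a mortality endpoint. With 35% + 15% deaths and weaning on day 9, the death = 0 difference is 0.50 × 19 − 9.6 = −0.1 days despite 10 points more mortality. VFD should therefore still be read beside the planned 28-day mortality table.
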